#### On-road driving assessment (RDA)

1.3.2

Complementary to the neuropsychological assessment, the RDA is considered as the “gold standard” in multiprofessional evaluation. The ecological nature of the on-road situation provides an opportunity to assess patients’ actual driving ability, enabling the adoption of compensatory strategies in the event of cognitive sequelae.

According to Michon’s hierarchical model, driving activity calls for three levels of skills and control, whose involvement varies according to the driver’s mental workload and the time constraints of the situation (Michon, 1985). The operational level involves a high time constraint (in the order of milliseconds) and a low cognitive workload, as it involves automatic action patterns. This level provides vehicle control, requiring quick and undemanding actions from the driver, such as manipulating the car controls or positioning the vehicle in the traffic lane. The intermediate tactical level involves a slightly lower time constraint during driving (in seconds) but calls on slightly higher-level cognitive processing systems, enabling the vehicle to be maneuvered in its environment. It is involved in situations requiring the driver to implement coping strategies that take into account both the perceived environment and the driver’s own driving goals (e.g., slowing down in heavy traffic or when visibility is poor). Finally, the strategic level involves a very low time constraint (in the order of minutes or even hours) but calls on very high-level cognitive functions, mainly upstream of the driving situation. In particular, it involves advance planning (before driving) and decision-making by the driver according to both external conditions (e.g., weather, traffic conditions) and the driver’s internal dispositions (e.g., fatigue, mood, and self-assurance). For example, the driver may choose to postpone departure to avoid traffic jams.

Functional analysis during RDA highlights these different processing levels, as well as the regulatory mechanisms adopted by the driver. Fuller proposes a dynamic model of driving (Task-Capability Interface: TCI) that focuses on the interaction between driver capability and task requirements (Fuller, 2005). According to the TCI model, the concept of task difficulty homeostasis consists in implementing compensatory strategies to maintain an average level of difficulty. The driver must not lose control of the vehicle (because the task is too complex), and must not lose vigilance (because the task is too simple), by constantly adjusting driving behavior. As a complement to neuropsychological assessment, the RDA assesses, in real-life situations, the implementation of coping strategies enabling safe driving ability to be maintained despite the presence of cognitive disorders.

Although recommended by the HAS, neuropsychological assessment and RDA are not mandatory. To date, the evaluation method recommended by the good practice guide has been applied by many rehabilitation centers. However, it must be noted that the tools and methods used differ considerably from one health center to another. Neuropsychological assessment practices vary in terms of the time devoted to assessment, the functions investigated, the choice of tests and the administration conditions. Similarly, for RDA, the route taken (rural, urban, expressway…) and the assessment methods (with or without an observation grid) also vary. In addition, the roles of each professional involved in the evaluation vary from one rehabilitation center to another, as well as the methods used to transmit the assessment results. The heterogeneous nature of these practices undoubtedly makes it difficult for the approved doctor to issue an opinion on the individual’s fitness to drive. The overall aim of this study is therefore to identify the most relevant methods and tools for assessing driving ability, in order to guide professionals’ practices in rehabilitation centers. In July 2023, the French Interministerial Road Safety Committee (Comité Interministériel à la Sécurité Routière, CISR) issued measures to “better detect, assess and monitor unfitness to drive” (CISR, 2023). Against this backdrop, this study aims to support public policy by harmonizing the multiprofessional evaluation recently made mandatory, so as to better inform the approved doctor’s opinion.

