##### Neuropsychological assessment

2.2.1.2

This assessment is carried out by a psychologist specialized in neuropsychology. It includes a series of validated standardized tests investigating attentional, executive and psycho-behavioral functions. The list of tests was co-constructed according to different criteria:- psychometric qualities (sensitivity, validity, reliability)- relevance established in the literature in relation to driving ability evaluation- availability and frequency of use in current practice (assessed through a survey of rehabilitation centers)- administration conditions (essentially non-verbal tests for use with patients with expressive aphasia; non-bimanual tests allowing inclusion of patients with hemicorporeal deficits; duration deemed acceptable and equipment easy to obtain and use).

The neuropsychological assessment lasts around 3 h, divided into two one-and-a-half-hour sessions, each with a five- to ten-minute break. The order of administration of the tests was established so as to alternate tasks according to their format (computerized vs. paper-and-pencil), their mental load (higher or lower), their sensitivity to fatigue, and the cognitive functions called upon. The standardized neuropsychological assessment protocol is described in the case report form. It includes the following tests: Alertness (TAP 2.3.1), Divided attention (TAP 2.3.1), Epworth scale, Trail-Making-Test (TMT), Go/Nogo (TAP 2.3.1), Basic Empathy Scale in Adults (BES-A), Neglect with central task (TAP 2.3.1), Tour of London (TOLDX 2^nd^ edition), Working memory difficulty level 3 (TAP 2.3.1), Sustained attention color-or-form version (TAP 2.3.1) and UPPS Impulsive Behavior Scale. Lastly, the Brain Injury Driving Self-Awareness Measure—BIDSAM (Gooden et al., 2017) is part of the neuropsychological assessment, but will be completed following the RDA.

For each test, the examiner collects raw and standardized scores (each participant’s performance is compared to the standard group). Based on this assessment, the neuropsychologist then issues an opinion (favorable, unfavorable or reserved) on the estimated compatibility between the participant’s cognitive functions and the return to driving.

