##### Main criterion: concordance between professional assessments

2.3.1.1

To meet the main objective, the concordance of the results of the neuropsychological assessment, RDA and multiprofessional evaluation will be studied in pairs (agreement between professional assessments). Each professional involved in the study will give a “favorable,” “reserved” or “unfavorable” opinion based on their practice. Evaluation criteria will correspond to cross-tabulated numerical values of results from each assessment tool studied (neuropsychological assessment, RDA and multiprofessional evaluation). “Reserved” opinions indicating driving restrictions will initially be classified as “unfavorable,” so that the results can be expressed as a binary Favorable/Unfavorable variable for each assessment. The RDA results will also include the number of driving instructor interventions on pedals, steering wheel and other car controls, using categorical variables. The values *a*, *b*, *c* and *d* (Table 1) will be used to perform the concordance test detailed in the next section (“Statistical analysis”).

**Table 1 tab1:** Evaluation criterion of the main objective for contingency table.

		Assessment x_i_	
		Favorable	Unfavorable
Assessment x_ii_	Favorable	*a*	*b*
	Unfavorable	*c*	*d*

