#### Statistical analysis

2.3.3

To meet the main and secondary A and B objectives, concordance tests will be used to verify that two independent abilities to resume driving measures (two tests) of the same modality—“Favorable” or “Unfavorable”—are equal. Concordance analyses between tests (binary variables) will be expressed in the form of concordance percentages, simple kappa coefficient and its 95% confidence interval. Analyses between TRIP (continuous variable) and other tests (binary variables) will be conducted using *t*-tests or Mann–Whitney tests depending on the TRIP score distribution. Multivariate regression will also be used to study measures’ concordance and prediction levels, for both objectives. It will be logistic or linear, depending on the studied variable (i.e., approved doctor’s opinion for objective A and TRIP results for objective B).

A sensitivity and specificity analysis of the approved doctor’s opinion will also be carried out. Performance metrics (Secondary Objective C) will be calculated from the confusion matrix values (Table 4):$$\mathrm{Accuracy:}\frac{RP+RN}{RP+RN+FP+FN}$$$$\mathrm{Sensitivity (Se):}\frac{RP}{RP+FN\text{.}}$$$$\mathrm{Specificity (Sp):}\frac{RN}{FP+RN}$$$$\mathrm{Positive predictive value (PPV) or Precision (Pr):}\frac{RP}{RP+FP}$$$$\mathrm{Negative predictive value (NPV):}\frac{RN}{FN+RN}$$

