#### Relevance of the neuropsychological assessment

3.1.1

- In the event of concordance between the neuropsychologist’s opinion and other assessments (RDA, multiprofessional, approved doctor’s opinion), the neuropsychological assessment can then be considered to be a good predictor of driving ability, particularly by shedding light on the driving restrictions to be recommended.- In the event of a discrepancy between the neuropsychologist’s opinion and other assessments (RDA, multiprofessional, approved doctor’s opinion), the neuropsychological assessment cannot be considered a reliable predictor of driving ability, in line with the mixed findings reported in the literature (Wolfe and Lehockey, 2016; McKay et al., 2016; Ortoleva et al., 2012). However, this assessment will still be of obvious interest for detecting any reduction in useful field of view, raising awareness of certain deficits, or suggesting rehabilitation options adapted to the person’s cognitive profile. The neuropsychologist’s role is decisive in the project to resume driving (Perna et al., 2021).- Neuropsychological tests whose scores are significantly correlated with the TRIP score can be considered the most predictive of driving ability. These results will help guide the choice of neuropsychological tools.

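### The rule that a discrepant neuropsychologist's opinion makes the neuropsychological assessment an unreliable predictor is not conditioned on the score-level results, although kappa on opinions also falls when cut-offs differ

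*Protocol article*

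**What the plan says.** **Aim.** Section 1.3.2 states: "The overall aim of this study is therefore to identify the most relevant methods and tools for assessing driving ability". The abstract announces concordance analysis at two levels, between professionals' opinions and between tools.

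**Main criterion (2.3.1.1).** Each professional gives a favorable, reserved or unfavorable "opinion based on their practice". Reserved is first pooled with unfavorable, "so that the results can be expressed as a binary Favorable/Unfavorable variable for each assessment". The same section describes these data in the language of tools: "Evaluation criteria will correspond to cross-tabulated numerical values of results from each assessment tool studied". Section 2.3.3 analyses them by "concordance percentages, simple kappa coefficient and its 95% confidence interval".

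**Scores.** In 2.2.1.2, for each test, "the examiner collects raw and standardized scores". The neuropsychologist then issues an opinion; the article states no rule that links scores to opinion. Under secondary criterion B (2.3.1.2.2), raw test results are correlated with the TRIP. Section 2.3.3 adds multivariate regression, with TRIP results as the outcome for objective B.

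**Conclusion rules (3.1.1).** The second bullet says that if the neuropsychologist's opinion disagrees with the other assessments, "the neuropsychological assessment cannot be considered a reliable predictor of driving ability". The third bullet is a separate rule: tests significantly correlated with the TRIP score count as the most predictive, and guide the choice of tools.

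**The concern.** A binary opinion has two ingredients: the information in the battery, and the point at which the clinician turns from favorable to unfavorable. Kappa between two opinions depends on both. The second bullet of 3.1.1 reads a low kappa as a fact about the first ingredient alone.

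Pooling reserved with unfavorable makes unequal cut-offs plausible. If one profession uses reserved more freely than another, its binary margin shifts with no change in what it knows about the patient.

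The two rules in 3.1.1 can also collide: individual tests may correlate significantly with the TRIP while the assessment built from them is declared unreliable. The article does not say how that would be resolved. The results are meant to underpin national recommendations (section 3) and to help bring invisible impairments into the fitness examination (3.4.2). A wrong verdict against the battery would work against that purpose.

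**Working it through.** The article gives no planning value for kappa and no expected favorable rates, so there is no figure of its own to reproduce here. Every input below is an assumption, chosen to show how far cut-offs alone can move kappa.

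**Model.** The battery and on-road ability are standard normal with correlation ρ. Each opinion is favorable above a cut-off. With p1 and p2 the favorable rates and a the probability that both are favorable:
- observed agreement Po = 1 − p1 − p2 + 2a
- chance agreement Pe = p1·p2 + (1 − p1)(1 − p2)
- kappa = (Po − Pe)/(1 − Pe)

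**1. Thresholds that vary between neuropsychologists.** Assume ρ = 0.8 and 50/50 opinions on both sides. Then kappa = (2/π)·arcsin(ρ). Normal threshold variation with SD s, in units of the patient SD, lowers the effective correlation to 0.8/√(1 + s²).

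| s | effective ρ | kappa |
|---|---|---|
| 0 | 0.800 | 0.637 × 0.927 = 0.59 |
| 0.25 | 0.776 | 0.637 × 0.888 = 0.57 |
| 0.5 | 0.716 | 0.637 × 0.797 = 0.51 |
| 1.0 | 0.566 | 0.637 × 0.601 = 0.38 |

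**2. Neuropsychologists uniformly stricter.** Assume ρ = 0.8, with 70% unfavorable for the neuropsychologist and 40% for the RDA.
- p1 = 0.30, p2 = 0.60, a = 0.286
- Po = 1 − 0.90 + 0.573 = 0.673
- Pe = 0.18 + 0.28 = 0.46
- kappa = 0.213/0.54 = 0.39

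With the milder split of 60% against 40% unfavorable, kappa is 0.50.

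**3. The limiting case.** Both assessments rank patients identically (ρ = 1) and the RDA is 70% favorable. Only the neuropsychologist's favorable rate changes.

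| Neuropsychologist favorable | kappa, ρ = 1 | kappa, ρ = 0.8 |
|---|---|---|
| 70% | 1.00 | 0.58 |
| 60% | 0.78 | 0.55 |
| 50% | 0.60 | 0.49 |
| 40% | 0.44 | 0.39 |
| 30% | 0.31 | 0.29 |

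At 50% against 70% with ρ = 1: Po = 0.80, Pe = 0.50, kappa = 0.30/0.50 = 0.60. At n = 100 the 95% interval is 0.44 to 0.76, so this kappa falls well short of 1 although the ranking is perfect.

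**4. What the discordant cells show.** In case 2, per 100 patients, about 60 − 28.6 = 31 are favorable on the RDA only and 30 − 28.6 = 1 on the neuropsychological opinion only. Uniform strictness therefore shows as a strong b versus c imbalance. The varying thresholds of case 1 leave b and c balanced, so that comparison alone would not reveal them.

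**The case against.** The case on the other side is substantial, and most of it stands.

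- **Agreement between opinions is a declared target.** The abstract and the heading of 2.3.1.1 say so, the study is described as real-life and exploratory, and the opinions feed the report that reaches the approved doctor. A reader might infer that the primary kappa is biased or the wrong estimand. The documents do not support that: it estimates what it is said to estimate.
- **Tool choice has its own analyses.** The correlations and regression with the TRIP do not use the neuropsychologist's cut-off. It would be wrong to say that the plan has no tool-level answer.
- **Decision habits are not among the heterogeneities listed in 1.3.2.** That section names test choice, duration, routes, grids, roles and reporting. A reader might infer that the study set out to remove threshold differences and failed; the text does not say so.
- **Discrepancies are not read mechanically throughout.** Section 3.1.2 looks at their direction and offers coping strategies as an explanation. Section 3.1.1 keeps other uses for the assessment.
- **Guidance on opinions may exist elsewhere.** The full protocol and case report form are not shown, so its absence cannot be asserted.
- **The magnitudes are assumed.** A threshold SD of 1.0 equals the whole patient SD, which is large.

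What this does not remove is the second bullet of 3.1.1. It moves from a discrepant opinion to a verdict on the assessment, does not mention cut-offs, and is not tied to the score-level results. Section 3.1.2 does not fill the gap: its explanation is used there to protect the value of the RDA.

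**Conclusion.** The point holds as a fault in a stated conclusion rule, not in the main criterion. A low kappa between opinions cannot distinguish a battery that carries little information from a good battery read with a different cut-off. Under an assumed latent correlation of 0.8, kappa goes from 0.59 to about 0.5 with moderate threshold differences and about 0.4 with large ones. Small differences hardly matter (0.57 at an SD of 0.25).

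These figures rest on a bivariate normal model and on favorable rates and threshold spreads that the article does not give; the real size is unknown. They show that the inference is unsafe. They do not show that the battery is good or that thresholds do differ between centers.

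**What to change.** 1. Keep the opinion kappa as the main criterion. State that it measures agreement between opinions, and amend the sentence in 2.3.1.1 that calls these opinions results of tools.
2. Report beside each kappa the favorable rate of each assessment and the b versus c comparison (McNemar).
3. Add a threshold-free analysis of the standardized scores already collected, for example the AUC of the number of impaired tests against the RDA opinion. Read it with the planned correlation and regression on the continuous TRIP, which do not depend on an RDA cut-off.
4. Reword the second bullet of 3.1.1: conclude that the assessment is unreliable only if this score-level evidence is also poor. Otherwise, report the discrepancy as possibly one of decision threshold or of compensation.

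A kappa from a mechanical pass/fail rule on the scores should not be the gate. It depends on an arbitrary cut and on the RDA raters' own threshold, so it can mislead in the same way.

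**Cost.** No new data; a few lines of analysis and a more cautious conclusion. The AUC will be fairly imprecise. For an assumed AUC A = 0.80 with 50 patients in each RDA group, the Hanley–McNeil variance uses A/(2 − A) = 0.667 and 2A²/(1 + A) = 0.711. It is [0.16 + 49(0.667 − 0.64) + 49(0.711 − 0.64)]/2500 = 0.00198. The SE is 0.0445, giving a 95% interval of about 0.71 to 0.89.

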## Method and analysis

2

### Study design and participants

2.1

The PREVAC study (driving skills assessment program) is a regional (Rhône-Alpes), multicenter, real-life prospective and exploratory study that is:- Cross-sectional for concordance and correlation analysis between the assessment tools available at the time of the approved doctor’s opinion;- Longitudinal for follow-up at 6 and 12 months after the approved doctor’s opinion, with data collected on participants’ driving habits and road risk.

This study is being carried out in collaboration with eight rehabilitation centers belonging to a regional network for caring and supporting people with npABI in the Auvergne-Rhône-Alpes region (Resaccel). The protocol has been designed, under the supervision of an international scientific committee, to ensure that the assessment is as standardized as possible between the healthcare centers taking part in the study (same equipment, same training, same procedure, same instructions, comparable on-road-assessment; the protocol and the case report form are available on OSF). At each center, a multiprofessional team was trained to assess the driving ability of their volunteer patients, according to the study protocol. Each team comprises a PRM doctor, a psychologist specialized in neuropsychology, an occupational therapist and a driving instructor. Within each rehabilitation center, an investigator monitors the study. Participants do not make the journey specifically for the study but as part of the follow-up offered to them by the centers. From there, they travel to the center using their usual means of transport.

Each rehabilitation center will recruit around 10 to 20 patients, up to a total of 100 participants. A post hoc sensitivity analysis was performed using G*Power Software Version 3.1.9.7 (Faul et al., 2007) to determine the minimum effect size that could be achieved with 100 participants. A post hoc power analysis for an independent-sample t-test was conducted assuming one-tailed testing. For effect size varying from large (d = 0.8) to small (d = 0.2), 80% power and alpha error probability of α = 0.05 a sample size interval of at least 12 to 156 participants is suggested. With a sample of 100 participants to be included in this study and 80% power the effect size is estimated at 0.25. Each participant must have a npABI and be between the ages of 21 and 65, in order to avoid confusing the issues of ageing and non-progressive acquired brain injury, people over 65 were excluded from the study and treated at their center for routine care. All participants must have held a Category B driving license (light vehicles) for at least 3 years and have driven a minimum of 10,000 km, so as not to assess novice drivers. They have been examined by the PRM doctor, who confirms that there are no contraindications to driving other than the pathology under study. They also gave their consent to take part in the PREVAC study. The ethical committee has classified this research as a non-interventional, involving no risk or constraint for participants, and in which all procedures are carried out in the usual way. They must not have a medical condition (other than npABI) that is incompatible with maintaining their driving license, according to the list of conditions mentioned in the decree of March 28, 2022. They must not have any oral comprehension disorders that can be perceived by the therapist, must not be pregnant (to avoid an interruption of pregnancy in the event of an accident and the resulting psycho-social and legal risks), and must not be under the influence of any Level 3 medication that could present a driving risk.

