### Analysis

2.3

Participant characteristics and assets will be described and compared. Reasons for refusing to participate will be collected. Descriptive statistics on participant characteristics will be presented. The characteristics of participants included will be compared with those of non-included participants in the eligibility register to ensure their representativeness. Quantitative variables will be described in terms of mean, standard deviation, median, interquartile range and extreme values. Qualitative variables will be described in terms of absolute frequency and percentage per modality. The alpha threshold for statistical significance is set at 5%; 95% confidence intervals will be presented. All the variables collected for people included in the study will be described. Missing data will not be replaced in this study and some participants might be secondary excluded from certain analyses. Sub-group analyses may be carried out, if statistically robust, depending on the number of fitted cars required and the conclusion of the medical examination.

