### Expected results

2.4

As this is an exploratory study, no assumptions are made concerning concordances between the different professional opinions. However, in light of the literature concerning coping strategies used by people with npABI, we can expect some results:

In the event of an unfavorable opinion on the neuropsychological assessment and a favorable opinion on RDA, we should observe high compensation scores on the TRIP, as well as a low score on the BIDSAM, indicating good metacognition enabling the driver to adapt their driving to their difficulties.

In the event of an unfavorable opinion on both the neuropsychological assessment and RDA, we should observe low compensation scores on the TRIP and a high score on the BIDSAM, indicating a low awareness of difficulties that does not allow the use of compensatory strategies.

TRIP compensation scores and the BIDSAM score should be good predictors of road risk.

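### The detectable effect for 100 participants is calculated one-tailed while the analysis reports 95% intervals; for the planned two-group TRIP t-test it is about 0.57 two-sided, not 0.25

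*Protocol article*

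**What the plan says.** Section 2.1 (Study design and participants) fixes the sample: "Each rehabilitation center will recruit around 10 to 20 patients, up to a total of 100 participants". It then reports what that number can detect. The test and its direction are given as "A post hoc power analysis for an independent-sample t-test was conducted assuming one-tailed testing". Over effect sizes from d = 0.8 down to d = 0.2 it states "80% power and alpha error probability of α = 0.05 a sample size interval of at least 12 to 156 participants is suggested", and for the planned sample "With a sample of 100 participants to be included in this study and 80% power the effect size is estimated at 0.25".

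Section 2.3 (Analysis) sets the error rate for the study: "The alpha threshold for statistical significance is set at 5%; 95% confidence intervals will be presented". It does not mention direction.

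Section 2.3.3 (Statistical analysis) says that the concordance analyses "will be expressed in the form of concordance percentages, simple kappa coefficient and its 95% confidence interval". A t-test, or a Mann–Whitney test if the distribution calls for it, is planned only where the continuous TRIP score is compared between the two categories of a binary opinion. That is a comparison of two independent groups. No analysis section declares a one-sided test.

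**The concern.** A 95% confidence interval corresponds to a two-sided 5% test; a one-sided 5% test corresponds to a 90% interval. The only statement of direction in the article is in the sample-size paragraph, and it does not match the interval level that the analysis will report. The detectable effect is therefore quoted at a more lenient error rate than the reported intervals imply, and looks smaller than it is.

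The TRIP comparisons matter because the Discussion uses TRIP results to judge whether the grid is a relevant tool. A reader who takes d = 0.25 at face value would believe that these comparisons can pick up small differences. A direction left undeclared in the analysis could also be settled after the results are known.

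**Working it through.** **Inputs from the article.** Alpha 0.05, power 0.80, one-tailed, d = 0.8 and 0.2 giving 12 and 156, and d = 0.25 at N = 100 (section 2.1); 5% with 95% intervals (section 2.3); a two-group TRIP comparison (section 2.3.3). **Assumption:** the favorable/unfavorable split is not given, so 50/50 (the best case), 70/30 and 80/20 are shown.

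**Formulas (exact noncentral t).**
- One-sample or paired: df = n − 1, noncentrality δ = d√n.
- Two independent groups: df = n1 + n2 − 2, δ = d√[n1·n2/(n1 + n2)].
- One-sided power = P(T(df, δ) > t at 0.95). Two-sided power = P(T > t at 0.975) + P(T < −t at 0.975).

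**Step 1. Reproduce the stated figures.** The test that the article names does not give them. One-sided, two independent groups need 21 per group (42 in total) for d = 0.8 and 310 per group (620 in total) for d = 0.2. A one-sided one-sample or paired test does give them: n = 12 (power 82.9%; 79.5% at n = 11), n = 156 (80.0%; 79.8% at n = 155), and a detectable d of 0.250 at n = 100.

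**Step 2. Effect of direction alone.** By the normal approximation, an effect with 80% power one-sided has two-sided power Φ(1.645 + 0.842 − 1.960) = Φ(0.527) = 70.1%. The exact value is 69.8%, both for the one-sample test at n = 100 and for two groups totalling 100. It does not depend on the split, because the detectable d adjusts to give the same δ on the same 98 df. The detectable effect rises by about (1.960 + 0.842)/(1.645 + 0.842) = 2.802/2.487 = 1.13.

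**Step 3. Detectable d at 80% power, N = 100.**

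| Test | One-sided 5% | Two-sided 5% |
|---|---|---|
| One-sample/paired, n = 100 | 0.250 | 0.283 |
| Two groups, 50/50 | 0.501 | 0.566 |
| Two groups, 70/30 | 0.546 | 0.617 |
| Two groups, 80/20 | 0.626 | 0.707 |

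The step from 0.25 to 0.50 comes from the test family: the multiplier of d is √100 = 10 for one sample of 100, but √(50·50/100) = 5 for two groups of 50. The step from 0.50 to 0.57 comes from direction. The two errors are separate and add up.

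**Step 4. Power at the stated d = 0.25, N = 100.**

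| Test | One-sided 5% | Two-sided 5% |
|---|---|---|
| One-sample/paired | 79.9% | 69.7% |
| Two groups, 50/50 | 34.3% | 23.6% |
| Two groups, 70/30 | 30.6% | 20.6% |
| Two groups, 80/20 | 25.7% | 16.8% |

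**Step 5. Where direction bites.** With 98 df the critical t is 1.661 one-sided and 1.984 two-sided. A TRIP comparison with t between these values in the expected direction would pass a one-sided 5% test, while its 95% interval would include zero.

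**The case against.** The article never says that the analysis is two-sided. Reporting 95% intervals can be a matter of presentation, the only interval tied to a named statistic is the one for kappa, and the direction of each test is often left to an analysis plan. This stands in part: two-sidedness is inferred from the interval level and from the absence of any one-sided declaration. But the article does state a direction in one place and an interval level in another, and the two do not match. If one-sided tests are intended, the text still has to say so and reconcile the intervals.

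The stakes are also limited, and this stands. The calculation describes what 100 participants could detect; it does not derive that number. The study is exploratory, and its main criterion is kappa.

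Three stronger readings are tempting, and the article does not support them.
- A reader might infer that the stated 80% power at d = 0.25 simply becomes 70%. That holds only for a one-sample or paired test, which is neither named nor planned.
- A reader might infer that borderline TRIP results are significant under one section and not under another. The sample-size paragraph sets no decision rule; only section 2.3 sets a threshold, with its direction undeclared.
- A reader might cite section 2.4 (Expected results), "As this is an exploratory study, no assumptions are made concerning concordances between the different professional opinions", as ruling out one-sided TRIP tests. That sentence concerns agreement between opinions, which is analysed by percentages and kappa. The same section goes on to state directional expectations for the TRIP compensation scores, so it gives no support either way.

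**Conclusion.** The point holds for the TRIP t-tests. The detectable effect is stated under one-tailed 5% testing, while the analysis section's 95% intervals correspond to two-sided 5% tests. Direction alone takes 80% power to about 70%, or equivalently raises the detectable effect by about 13%. For the test that is named and planned, the two-sided figure for 100 participants is about 0.57 at best, more than twice the stated 0.25, and 0.62 or 0.71 at the less even splits.

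This rests on reading the 95% intervals as two-sided 5% testing, on the assumed splits, and on complete data for 100 participants. It says nothing about the precision of kappa. The correction is worth making because it repairs a printed figure at almost no cost.

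**What to change.** State once, for both section 2.1 and section 2.3, that tests are two-sided at 5%, consistent with the 95% intervals. Remove the reference to one-tailed testing.

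Restate the detectable effect for the two-group TRIP comparison, naming the test and the assumed favorable/unfavorable split: for example, d of about 0.57 at 50/50, 0.62 at 70/30 and 0.71 at 80/20, with 100 participants and 80% power. Replace the 12 to 156 range on the same basis: two-sided, two equal groups need 26 per group (52 in total) for d = 0.8 and 394 per group (788 in total) for d = 0.2. Naming the test is essential, because changing direction alone would print 0.28 in place of 0.25 and leave the larger error standing.

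Keep 100 participants. The cost is wording and a less favourable stated figure; no extra participants, visits or data are needed.
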